### Participant timeline {13}

The flow of participant involvement and descriptions of study visit procedures are described in Fig. 1. Participants will be screened by phone to determine initial eligibility. Within 30 days of initial eligibility confirmation, participants will complete an in-person clinical screening visit to further confirm eligibility. If the candidate remains eligible, they will be invited to complete baseline and randomization visits within 30 days of screening. All additional visits will occur biweekly for 8 weeks and follow the procedure flow according to Fig. 1 and Table 3.

### Sample size {14}

A sample size of at least 12 participants per group provides 80% power to detect ≥50% difference in the proportions of participants experiencing laboratory abnormalities or adverse events at a threshold of *α* = .05 by *χ*^2^ test. This sample size, at *n* = 12 per arm, provides >90% power using 2-sided *t*-tests to detect a mean change of 0.25–0.5pg/mL in TNF-α in the treatment arm according to preliminary data from previous pilot studies. Accounting for attrition up to 25%, we will randomize up to 32 participants. Attrition during the phase I trial was 10% [15].

### Recruitment {15}

Participants will be recruited from the Portland, OR, area via word-of-mouth and via posted flyers at the institution’s clinic, local shops, and restaurants. Flyers will also be posted through online advertisements on a weekly basis. Indirect recruitment will occur through presentation at medical conferences at local support groups, such as the Northwest Chapter of the Crohn’s and Colitis Foundation, at which flyers will be available for attendees. Advertisements will also be placed through the Crohn’s and Colitis Foundation’s website and distributed through local chapter newsletters. The NUNM electronic health records system will be leveraged to generate a list of candidate participants based on ICD-9/10 codes with recruitment via email or direct mail. Oregon Health and Sciences University (OHSU) and its Oregon Clinical and Translational Research Institute (OCTRI) will be similarly leveraged to generate a list of candidate participants for direct recruitment.

## Assignment of interventions: allocation

### Sequence generation {16a}

The randomization sequence will be computer-generated and stratified according to biological sex to randomize 50% male and 50% female participants in each group.

### Concealment mechanism {16b}

A staff member of the Helfgott Research Institute uninvolved with the trial will maintain allocation concealment and create 32 sequentially numbered, opaque, and sealed envelopes containing the individual group assignments according to the randomization sequence.

### Implementation {16c}

Envelopes will remain maintained in a locked cabinet in a locked document room until the baseline visit when randomization occurs by one of the clinical investigators or coordinators. Thus, allocation will be concealed from study principal investigators (PI), coordinators, clinical investigators, participants, and statisticians until each participant is randomized.

## Assignment of interventions: blinding

### Who will be blinded {17a}

Blinding will be accomplished through multiple methods. Trained staff uninvolved in trial operations or analyses will produce a group code, receive and label product bottles accordingly, and generate stratified randomization sequences using freely available online software. To avoid any speculation about group allocation changes since the previous phase I trial, randomization group labels were altered to be “X2” and “Y1” (versus “A” and “B”). Upon randomization, participants will be assigned a new alpha-numeric ID reflecting their enrollment status. All parties involved in trial conduct will remain blinded until the primary trial analyses are deemed complete by all trial PIs; only then will group assignment be revealed. As secondary analyses are divided between collaborating sites, those directly involved with measurements and analyses will remain masked until these measures are completed and deemed final.

### Procedure for unblinding if needed {17b}

Unblinding will be permissible in the case of a serious adverse event requiring hospitalization or resulting in fatality, or if the data and safety monitoring board (DSMB) requires it upon regular review.

## Data collection and management

### Plans for assessment and collection of outcomes {18a}

Data collected from all participant interactions will be recorded on paper case report forms (CRFs) with electronic transcriptions stored in REDCap® [21, 22]. Physical data will be stored in a locked cabinet, in a locked document room, or in a building accessible only via badge or key. Electronic data will be stored in a de-identified manner and entered on a password-protected device by study staff into REDCap®. All data will be collected by study staff by verbal query or physical assessment other than the PROMIS-29 questionnaire which the patient will self-report directly into REDCap® on a password-protected tablet. All specimens will be labeled using a convention that includes participant ID, visit number, date stored, and specimen type.

Hematologic safety parameters in this study include those associated with liver function (AST, ALT, alkaline phosphatase, bilirubin, and GGT); kidney function (eGFR, BUN, creatinine, and BUN:Cr); general hematology (red blood cell count, white blood cell count, hematocrit, and hemoglobin); and electrolytes (sodium, potassium, calcium, and chloride). Spontaneous, self-reported, and serious adverse events will also constitute the safety and tolerability profile of XN. Retention, intervention adherence, and self-reported quality of life, measured through the Patient-Reported Outcomes Measurement Information System 29-item questionnaire (PROMIS-29) [23], will be considered measures of tolerability. All parameters will be collected at each visit and intervention adherence will be monitored at 4 weeks from baseline and at closeout.

Clinical activity will be evaluated using the Crohn’s Disease Activity Index (CDAI). The CDAI is a validated index based on clinical observations, laboratory values, and patient-reported outcomes [24, 25]. While there remains some controversy over the use of the CDAI, it correlates with other accepted indexes of clinical activity and some patient-reported subsets and further correlates with endoscopic activity indexes [26]. Abdominal examinations for masses will be performed by a licensed clinician.

Hematologic specimens will be collected by a trained phlebotomist or licensed clinician at the Helfgott Research Institute. Specimens used to establish safety parameters (CBC and CMP) will be analyzed through NW Quest Diagnostics® (Seattle, WA, USA). Hematologic specimens for serum and plasma analysis will simultaneously be collected and centrifuged at 1450 times *g* for 15 min within 2 h of collection. Plasma samples collected in lithium heparin-coated vacutainer tubes will be separated by serial 500-μL aliquots and stored in 1-mL graduated DNase-free, RNase-free, pyrogen-free cryovials (Simport, Beloeil, Quebec) at −70°C at the study site. Circulating concentrations of inflammatory biomarkers, including tumor necrosis factor-α and interleukins (e.g., IL-1, 10, 12, and 17); intestinal permeability markers (e.g., CD14 and intestinal fatty acid binding protein); and markers of endotoxemia (i.e., lipopolysaccharide and its binding protein) will be assessed by flow cytometry-based multiplex assays [27], enzyme-linked immunosorbent assay (ELISA) [28], and Limulus amebocyte lysate assay [29, 30], respectively.

Sodium citrate-anticoagulated blood samples (20 mL/participant) will be processed within 2 h of collection for platelet studies at baseline, week 4, and closeout. A small volume of whole blood (50 μL) from each sample will be prepared for flow cytometry analysis as previously described [31, 32]. For biochemical studies, platelets will be purified from whole blood samples by centrifugation and resuspended in a modified HEPES/Tyrode (H-T) buffer as previously described [32]. Washed platelet samples will be treated prior to lysis, flash frozen, and stored at −80°C. Subsequent analyses will measure specific biochemical and intracellular signaling responses to assess the effect of XN on platelet function using Western blot and by quantitative mass spectrometry, as previously described [32].

All stool samples are expected to be collected the morning of each visit from a single bowel movement; however, in instances where participants collect stool samples the night before their visit, they will be instructed to place all samples in a residential freezer prior to transportation to the research facility to preserve specimen integrity. Fecal calprotectin (FCP) will be quantified using the Calprotectin ELISA Assay kit (Epitope Diagnostics, Inc., San Diego, CA, USA). Gut microbial and bile acid compositions will be determined from the OmniGene®GUT Kit (DNA Genotek, Ottawa, ON, Canada) and subsequent procedures as described in detail by partner sites [33, 34].

Analytes of XN will be collected at each visit beginning at baseline via circulating plasma, a 24-h urine collection, and stool samples to establish a longitudinal profile of metabolism and isomerization. Identification and quantification of XN and its metabolites, including isoxanthohumol, 6-prenylnaringenin, 8-prenylnaringenin, O-desmethylxanthohumol, dihydro-*O*-desmethylxanthohumol, and α,β-dihydroxanthohumol, will be achieved by using ultra-high-performance liquid chromatography-triple quadrupole time-of-flight mass spectrometry (LC-MS/MS) as previously described [35, 36]. Plasma samples, and stool samples without fixatives, will be collected and stored according to the processes outlined above. Urine specimens will be separated from the 24-h sample following homogenization in serial 1-mL aliquots to be stored in 1-mL graduated DNase-free, RNase-free, pyrogen-free cryovials (Simport, Beloeil, Quebec) at −70°C at the study site.

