### Objectives {7}

The main objective of the phase II trial is to determine the safety and tolerability of 24 mg/day of orally delivered XN compared to a placebo over 8 weeks in a group of adults with active CD. Secondary objectives of this study include assessing the impact of XN on the clinical activity of CD, inflammatory biomarkers that are often elevated in patients with CD, the composition of the gut microbiome in patients with CD compared to healthy adults, and the hemostatic function of platelets, as well as measuring the metabolic pathways and metabolite concentrations of XN. A summary of objectives and outcomes can be found in Table 1.

**Table 1 Tab1:** Objectives and outcomes

Objectives Assessment of:	Measures	Method of assessment
*1. Safety and tolerability*	i. RBC, WBC, platelets ii. eGFR, electrolytes, BUN:Cr, AST, ALT, GGT, alkaline phosphatase, bilirubin iii. Heart rate, blood pressure, temperature, body mass index (BMI) iv. Adverse events and quality of life	i. Complete blood count (CBC) ii. Comprehensive metabolic panel (CMP) iii. Vital sign measurement iv. Adverse event monitoring and PROMIS-29 questionnaire
*2. Disease activity*	i. Clinical activity	i. Crohn’s Disease Activity Index (CDAI)
*3. Inflammation*	i. Inflammatory cytokines ii. Fecal calprotectin	i. Serum or plasma analysis ii. Fecal analysis
*4. Gut permeability and endotoxemia*	i. CD14, lipopolysaccharide (LPS) and LPS-binding protein, intestinal fatty acid binding protein	i. Plasma analysis
*5. Platelet function*	i. Platelet signaling, secretion, and procoagulant activity	i. Proteomic analysis ii. Flow cytometry
*6. Microbiome and bile acid compositions*	i. Metagenomic DNA sequencing and taxonomic profiling ii. Proteomic characterization iv. Bile acid profiling	i. Stool analysis ii. Activity-based proteomic assay iii. Plasma analysis
*7*. *Metabolic profile of XN*	iv. Xanthohumol (XN), isoxanthohumol, 6-prenylnaringenin, 8-prenylnaringenin, desmethylxanthohumol (DXN), dihydro-desmethylxanthohumol (DDXN)	iv. 24-h urinalysis, plasma analysis, stool analyses

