#### Hypotheses

We hypothesize 24 mg/day of XN will be safe and tolerable in an adult population with active CD over an 8-week period. This will be supported by observing no greater than a 50% greater frequency in differences of laboratory abnormalities or adverse events in the XN group. We also hypothesize XN will improve the clinical activity and reduce inflammatory biomarker concentrations in CD, demonstrate a metabolite profile different than that of healthy adults, and generate a specific gut microbiome signature. These comparisons will be achieved by measuring data against that from the phase I clinical trial of the same interventional product and period.

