### Outcomes {12}

The primary outcomes of the phase II trial include changes in laboratory toxicology measures, vital signs (blood pressure and heart rate), and AEs (Table 1). Assessment of laboratory measures to determine safety includes review for new-onset abnormalities (confirmed with repeat testing at the following clinical visit or as soon as possible following closeout, as applicable), including new-onset clinically significant elevation of liver function tests [aspartate transaminase (AST), alanine transaminase (ALT), bilirubin or alkaline phosphatase], new-onset anemia, elevations in creatinine, and/or reductions in estimated glomerular filtration rate (eGFR). Elevations of liver function tests will be considered “significant” if (1) abnormal per laboratory reference ranges and (2) represent a 25% deviation from previously observed values. New-onset anemia will be considered “significant” if (1) hemoglobin < 14 g/dL (140 g/L), hematocrit < 42% (< 0.42), or RBC < 4.5 million/mcL (< 4.5 × 10^12^/L) (for men); or hemoglobin < 12 g/dL (120 g/L), hematocrit < 37% (< 0.37), or RBC < 4 million/mcL (< 4 × 10 ^12^/L) (for women); *and* (2) values represent a 10% change or more from *baseline* values; *and* (3) values remain abnormal with repeat testing within 2 weeks. This threshold reduces reporting of new “borderline” abnormal values for participants with “high normal” baseline values. For elevations of creatinine, “significant” will be evaluated as greater than a 20% increase from *baseline* values, whereas reductions in eGFR will be considered as “significant” if greater than a 20% decrease from *baseline* values. A brief clinical interview will be conducted and recorded for all laboratory abnormalities not present at baseline to provide context, i.e., new-onset anemia tied to increased diarrheal episodes, etc. Serum calcium, potassium, and sodium; ɣ-glutamyl transferase (GGT); and blood urea nitrogen (BUN) to creatinine ratio (BUN:Cr) will also be collected to monitor electrolyte balance and provide additional measures of liver and kidney function, respectively.

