The primary endpoint for laboratory values and vital sign measurements will be mean change from baseline to week 8, with changes also compared between groups from baseline to each additional follow-up visit (i.e., 2, 4, and 6 weeks). The frequency of new-onset or worsening laboratory values will be reported within groups throughout the trial at each biweekly visit. AEs and event severity will be reported as new-onset or worsening events spontaneously and at each biweekly visit. Together, these outcomes will provide a profile of safety and tolerability of 24mg XN for 8 weeks compared to placebo.

Secondary and exploratory outcomes include clinical disease activity, systemic inflammation (e.g., IL-10), intestinal permeability (e.g., intestinal fatty acid binding protein) and endotoxemia (e.g., LPS), platelet function, stool microbiome and bile acid composition, and the metabolic profile of XN in humans over 8 weeks. Each measurement will be collected at every biweekly clinical visit and compared between groups as mean change from baseline within groups and compared between groups at each follow-up visit. The primary endpoint for each secondary and exploratory outcome will be considered exploratory and reported as mean change within groups at week 8 from to baseline and compared between groups at each follow-up visit. The measurements to support these outcomes are outlined in Table 1.

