### Methods in analysis to handle protocol non-adherence and any statistical methods to handle missing data {20c}

Given the safety-oriented and mechanistic nature of the trial, all analyses will be conducted per protocol; however, as a sensitivity analysis, missing laboratory data will be imputed by multiple imputation to assess the robustness of study results.

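### Retention and adherence are named as tolerability measures but are missing from the tolerability criterion, the primary outcomes and Table 1, and the per-protocol rule removes the participants who would show a problem

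*Protocol article*

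**What the plan says.** Tolerability is half of the main objective (Objectives {7}). The article describes how it will be judged in several places.

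- **Hypotheses.** The hypothesis is "We hypothesize 24 mg/day of XN will be safe and tolerable in an adult population with active CD over an 8-week period". Its only numeric support is "no greater than a 50% greater frequency in differences of laboratory abnormalities or adverse events in the XN group".
- **Outcomes {12}.** "The primary outcomes of the phase II trial include changes in laboratory toxicology measures, vital signs (blood pressure and heart rate), and AEs". The section then states: "Together, these outcomes will provide a profile of safety and tolerability".
- **Table 1, objective 1 (safety and tolerability).** Besides blood counts, chemistry and vital signs, it lists "Adverse events and quality of life".
- **Plans for assessment and collection of outcomes {18a}.** "Spontaneous, self-reported, and serious adverse events will also constitute the safety and tolerability profile of XN". The next sentence adds retention, intervention adherence and PROMIS-29, which "will be considered measures of tolerability".
- **Statistical methods {20a}.** PROMIS-29 has a between-group Welch's t-test. Retention and adherence are not mentioned.
- **Non-adherence and missing data {20c}.** "all analyses will be conducted per protocol". The only sensitivity analysis is multiple imputation of missing laboratory data.
- **Discontinuation {11b} and adherence {11c}.** Participants who report dosing deviations are treated as non-adherent and withdrawn. Adherence means more than 80% of expected doses, checked by capsule count at week 4 and closeout.

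**The concern.** Leaving the trial and stopping the capsules are the most direct signs that a product is poorly tolerated, and {18a} names both. The places that say what will support the conclusion do not use them. The stated analysis rule then works against them, because a per-protocol set is formed by removing people who left or did not take the product. Retention cannot be measured in such a set, and adherence in it is high largely because of how it was selected.

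At stake is the statement that XN is tolerable. A participant who stops because the capsules are unpleasant, and has no graded adverse event recorded, is a tolerability failure under {18a}. The same participant adds nothing to the criterion under Hypotheses or to the primary outcomes.

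**Working it through.** **Step 1: coverage of each measure.**

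| Measure | Hypotheses criterion | Primary outcomes {12} | Table 1, objective 1 | {18a} | Between-arm comparison stated |
|---|---|---|---|---|---|
| Laboratory abnormalities | yes | yes | yes | yes | yes {20a} |
| Vital signs | no | yes | yes | no | yes {12} |
| Adverse events | yes | yes | yes | yes | yes {22} |
| PROMIS-29 | no | no | yes | yes | yes {20a} |
| Retention | no | no | no | yes | none |
| Adherence | no | no | no | yes | none |

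Only retention and adherence appear in {18a} and nowhere else in the table.

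**Step 2: the plan's own numbers.** Sample size {14} asks for 12 per arm, allows 25% attrition and randomizes up to 32: 24 / (1 − 0.25) = 32, which reproduces. With 1:1 allocation this is 16 per arm, and planned attrition is 0.25 × 32 = 8 participants. The article does not say how those 8 may fall between the arms.

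**Step 3: an uneven split within that allowance (assumed).** Let 7 of 16 leave or stop on XN and 1 of 16 on placebo, 8 in total.

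- Proportions: 7/16 = 43.8% and 1/16 = 6.3%, a difference of 37.5 points.
- Fisher's exact test, two-sided: the probability of 7 or 8 of the 8 leavers falling in one given arm is [C(16,7) × C(16,1) + C(16,8)] / C(32,8) = (183,040 + 12,870) / 10,518,300 = 0.0186. Doubling for the symmetric tail gives p = 0.037.
- Newcombe 95% interval: the Wilson limits are 0.231 to 0.668 for 7/16 and 0.011 to 0.283 for 1/16. Lower limit: 0.375 − √[(0.4375 − 0.231)² + (0.283 − 0.0625)²] = 0.07. Upper limit: 0.375 + √[(0.668 − 0.4375)² + (0.0625 − 0.011)²] = 0.61.

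**Step 4: the same trial under the stated criterion.** The completers are 16 − 7 = 9 on XN and 16 − 1 = 15 on placebo. Assume one third of completers in each arm have a laboratory abnormality or adverse event: 3/9 and 5/15, both 33.3%. The excess on XN is 0%, so the criterion is met.

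**Step 5: how far this depends on the leavers' events.** Suppose instead that every leaver had a recorded event and all randomized participants are counted. XN then has (3 + 7)/16 = 62.5% and placebo (5 + 1)/16 = 37.5%. The relative excess is 62.5/37.5 − 1 = 67%, above 50%. The absolute difference is 25 points, below 50. So even with complete adverse event capture, whether the criterion reacts depends on the analysis set and on how the 50% is read.

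**Step 6: what a test of retention could do.** With 16 per arm, Fisher's test at 0.05 has about 36% power for 10% vs 40% dropout and about 58% for 10% vs 50%. The 10% is the phase I attrition quoted in {14}; the other rates are assumed. A non-significant p-value would say little, so the estimate and interval should lead.

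**The case against.** The strongest reply is that {18a} does not oppose the other sections. The sentence just before the one on retention counts adverse events towards safety and tolerability, so the lists overlap and {18a} is simply the fullest. That is correct. A reader might infer that the article holds rival definitions of tolerability, but the text supports only incomplete coverage. Nor is quality of life left out: PROMIS-29 is in Table 1 and has a between-group test.

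A second reply is that a table of withdrawals and capsule counts by arm belongs in an analysis plan or full protocol that is not shown. This would stand if the article were merely silent. However, it fixes one rule for all analyses, per protocol, and that rule conflicts with using retention and adherence as outcomes.

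Third, the per-protocol set is not defined, and nothing says retention would be computed within it. This stands as a limit on the claim. A reader might infer that both measures are bound to be near 100% in each arm. The documents support only that, on a literal reading, adherence is high largely by selection and the leavers are excluded.

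Fourth, many who stop would report a symptom. Adverse events are asked about with a structured questionnaire at each biweekly visit, accepted spontaneously and compared between arms {22}, and new symptoms are followed up {30}. This also stands. A reader might infer that the 7 to 1 split becomes no events against no events under the criterion. That holds only if the leavers have no recorded adverse event or the per-protocol set drops their events, and the article states neither.

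Finally, the Hypotheses section says its criterion will support the hypothesis. It does not set a formal rule for declaring XN tolerable, and the study team and DSMB also judge attribution case by case.

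**Conclusion.** The point holds for retention and adherence only. Both are named as tolerability measures in {18a}, and both are absent from the Hypotheses criterion, the primary outcomes and Table 1. The per-protocol rule in {20c}, together with withdrawal for reported dosing deviations in {11b}, would on a literal reading exclude the participants in whom poor tolerability shows.

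A difference in leaving as large as 44% vs 6% (37.5 points, 95% interval about 7 to 61, p = 0.037) fits within the planned attrition and need not count against the stated criterion. The illustration assumes 16 per arm, a 7 to 1 split and equal event rates of one third among completers. It is weaker where leavers have recorded adverse events that are kept in the analysis. It shows what the plan permits and does not predict what will happen. The defect lies in wording and analysis set; the data needed are already being collected.

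**What to change.** 1. Reconcile Hypotheses, Outcomes {12}, {18a} and Table 1 so that retention to week 8 and capsule-count adherence (>80% of expected doses, as in {11c}) are listed as tolerability outcomes with adverse events and PROMIS-29.
2. In {20c}, exempt retention and adherence from the per-protocol rule and take all randomized participants as the denominator.
3. Report each by arm with the difference and its 95% confidence interval, next to any statement that XN is tolerable. A Fisher p-value may be added as supportive only, given the low power.

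The cost is a few sentences and two 2x2 tables. Capsule counts are already planned, and withdrawals are known in any case. Sample size, visits and trial procedures do not change.
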